#### Non-compliance (only in intervention arm)

Number of episodes per patient and in the cohort where a BG measurement is not followed up within 30 minutes by a request for GS2 advice.

- Data will be extracted for analysis from the GS2 database.

Number of episodes per patient and in the cohort where pumps were not set within 30 min according to a GS2 advice accepted by the nurse (nurse did not notice, was busy, forgot, or misinterpreted advice = true errors). Data will be extracted for analysis from the GS2 database.

Number of advices given by GS2 which were accepted, accepted with modification and rejected. Data will be extracted for analysis from the GS2 database.

#### Prediction error of BG

For each measured BG a prediction is made by GS2's metabolic model and for each of the following measured BGs the difference between natural logarithm of the measured and the predicted BG is calculated. The differences are placed in one-hour wide bins according to the prediction time. The prediction time is the time elapsed between the BG measurement from which the prediction is made and the later measured BGs. For each one-hour bin the root mean square of the logarithmic differences in that bin is plotted against the average prediction time in the bin. An example is given in the figure below from which it for example can be seen that the one-hour prediction error is about 14%. The curve which is fitted to the plot will be used as the BG prediction error and it is used to compare the quality of GS2 BG prediction with predictions by other metabolic models in the literature [35]. It is also used by GS2 to determine when the predictive error has become so large that a new BG measurement is required. The data required for the calculation of the BG prediction error will be extracted for analysis from the GS2 database.

[figure not shown]

*The Root Mean Square of the prediction error for each one hour prediction interval.*

### **9.2.4 Assessment of safety outcomes**

#### Hypoglycemia

- Overall number and percentage of mild ( $\leq 3.2$  mmol/l) and severe ( $\leq 2.2$  mmol/l) hypoglycaemic events per patient and in the cohort
  - All hypoglycaemia episodes will be reported in the eCRF, number and percentage will then be calculated.

- Number and percentage of mild ( $\leq 3.2$  mmol/l) and severe ( $\leq 2.2$  mmol/l) hypoglycaemia events due to non-compliance (only in intervention arm)
  - o All hypoglycaemia episodes will be reported in the eCRF. Then, those data will be analysed jointly with the “non-compliance” outcomes.

#### Hyperglycemia (> 8.5 mmol/l)

- Time to normalize blood glucose (the first two consecutive values values  $\leq 8.5$  mmol/l as indicator for normalization)
  - o All the BG measurements will be reported in the eCRF with the time of the measurement. The time to normalize BG will be analysed from those data for the control and the intervention group.
- Percentage of time in the ICU with hyperglycaemia (BG > 8.5 mmol/l) before and after normalization per patient and in the cohort
  - o BG values are considered constant from one measurement to the next. Percentage of time in the ICU with hyperglycemia is defined as cumulative time with BG > 8.5 divided by the time spent in the ICU.
- Percentage of time in the ICU with hyperglycaemia (BG > 8.5 mmol/l) before and after normalization per patient and in the cohort due to non-compliance (only in intervention arm)
  - o Percentage of time with hyperglycemia will be analysed jointly with the “non-compliance” outcome.
- Number of hyperglycaemic episodes after normalization per patient and in the cohort
  - o All hyperglycaemic events will be record in the CRF. Those data will be analysed jointly with the “Time to normalize BG” outcome.
- Number of hyperglycaemic episodes after normalization per patient and in the cohort due to non-compliance (only in intervention arm)
  - o All hyperglycaemic events will be record in the CRF. Those data will be analysed jointly with the “Time to normalize BG” and the “non-compliance” outcome.

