| Outcome(s): | 
Primary outcome:
Time-in-target (BG in range: 5.0 to 8.5 mmol/l) per patient and in the cohort.
 
Other outcomes:
Concerning safety:
 
Hypoglycaemia
 
 
- Overall number and percentage of mild (<math>\leq 3.2</math> mmol/l), and severe (<math>\leq 2.2</math> mmol/l) hypoglycaemic events per patient and in the cohort
 
- Number and percentage of mild (<math>\leq 3.2</math> mmol/l), and severe (<math>\leq 2.2</math> mmol/l) hypoglycaemia events due to non-compliance (only in intervention arm)
 
 
Hyperglycaemia (> 8.5 mmol/l)
 
 
- Time to normalize blood glucose (2 values between 5.0 and 8.5 mmol/l as indicator for normalization)
 
- Percentage of time in the ICU with hyperglycaemia (BG > 8.5 mmol/l) before and after normalization per patient and in the cohort
 
- Percentage of time in the ICU with hyperglycaemia (BG > 8.5 mmol/l) before and after normalization per patient and in the cohort due to non-compliance (only in intervention arm)
 
- Number of hyperglycaemic episodes after normalization per patient and in the cohort
 
- Number of hyperglycaemic episodes after normalization per patient and in the cohort due to non-compliance (only in intervention arm)
 
 
Non-compliance (only in intervention arm)
 
 
- Number of episodes per patient and in the cohort where a BG measurement is not followed up within 30 minutes by a request for Glucosafe 2 advice.
 
- Number of episodes per patient and in the cohort where pumps were not set within 30 min according to a Glucosafe 2 advice accepted by the nurse (nurse did not notice, was busy, forgot, or misinterpreted advice = true errors)
 
- Number of advices given by GS2 which were accepted, accepted with modification, or rejected
 
 
Concerning effectiveness:
 
Achievement of nutritional goals.
 
 
- The protein goal is met (e.g. 80-100% of accumulated target)
 
- The caloric goal is met (e.g. 80-100% of accumulated target)
 
- Energy debt at the end of the stay
 
- Protein debt at the end of the stay
 
 
Workload:
 
 
- Frequency of BG measurements per patient and in the cohort
 
- Frequency of adjustments of insulin and nutrition pump settings
 
 
Glycaemic "variability":
 
 
- Mean and standard deviation (SD) of BG
 
- Maximum of daily BG difference
 
 
Prediction of blood glucose:
 
Prediction error as a function of time elapsed since last BG measurement, per patient, per cohort.
 |

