| Design:                         | 
Randomized controlled study with an intervention group, a control group; a historical control group will also be studied:
 
 
- Intervention group: Glucosafe 2 is used until the patient is discharged from the ICU or for a maximal follow-up of 15 days or when he/she starts eating (voluntary feeding). Number of patients: 71
 
- Control group: Standard care according to local ICU protocols (Geneva-HUG). The maximal follow-up is of 15 days or when he/she starts eating (voluntary feeding). Number of patients: 71.
 
- Historical control group: retrospective data from a random sample of 71 patients exposed to the standard care regarding nutrition support and glycaemic control and recruited before the beginning of the pilot study in order to minimize the “cross-over” effects and to confirm the predictive accuracy of Glucosafe2. Historical controls’ data will be retrospectively harvested from the patients’ computerized record. They will be recruited within 2 years before the trial start.
 
 |
| Inclusion / exclusion criteria: | 
Inclusion criteria:
 
All patients <math>\geq 18</math> years old admitted in adult ICU- Geneva with
 
 
• An expected length of stay <math>\geq 72</math>h
 
• At least 1 blood glucose (BG) measurement <math>\geq 10</math> mmol/l or 2 BG measurement <math>\geq 8.5</math> mmol/l
 
• Informed Consent signed by the subject/ legal representative, except for patients in the historical control group
 
 
Exclusion criteria:
 
 
• Lack of legal consent or consent withdrawn, except for patients in the historical control group
 
• Pregnant or breast feeding
 
• Diabetic ketoacidosis or hyperosmolar state
 
• Oral feeding
 
• Fulminant hepatic failure
 
• Medically contraindicated to receive rapidly acting insulin by intravenous (iv) infusion or iv injection
 
                                                                                                                                             |

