| Measurements and procedures: | 
Screening will be done every day (Monday to Friday). Eligible patients will be randomly allocated to either intervention or control group. Before inclusion, all patients will be treated according to the ICU- Geneva Protocols.
 
Collected data:
 
Baseline at study inclusion day
 
 
- Body mass, height and body mass index (BMI)
 
- Age, gender
 
- Date and time of admission in the ICU
 
- Primary diagnostic
 
- Known chronic illness (diabetes, acute kidney injury (AKI), pancreatitis, tumor, etc.).
 
- Medication influencing glycaemia (oral antidiabetics' insulin, steroids, prednisone, etc.).
 
- Renal and hepatic status
 
- Glycaemia and lactate
 
- Vitals
 
- Severity score (APACHE II, SAPS II) at ICU admission
 
 
Daily data from inclusion day (maximum follow up of 15 days)
 
When possible – Following routines measurement.
 
 
- Glucose measurements
 
- Other laboratory: lactate, CRP, sodium (Na), potassium (K), glycohemoglobin (HbA1C), urea, creatinine, glomerular filtration rate (GFR), protein, albumin, ASAT, ALAT, phosphatase alkaline, γ-glutamyltranspeptidase (GGT), bilirubin
 
- Any events (intubation, extubation, length of surgery, infusions, cardiac events, infections, requirement for red blood cell (RBC) transfusion, hemodynamic rate (HR), organ failure)
 
- Vitals (blood pressure, temperature, heart rate etc.)
 
- Antibiotics usage
 
- Vasopressor
 
- Steroids
 
- Propofol® for sedation
 
- Glucose perfusion
 
- Insulin therapy including boluses.
 
- Body weight, BMI, Ideal body weight (if needed), presence of oedema.
 
- Energy expenditure (IC or predictive formula)
 
- Energy and protein targets over the day
 
- Prescription and administration (ml of product, kcal and grams of protein).
 
- Daily water balance
 
- Diuresis
 
- Diarrhoea, constipation
 
- Nausea, Vomiting, gastric residual
 
- Physical therapy
 
- Medical Research Council Scale (MRC Scale)
 
 
Upon ICU leave
 
 
- Duration of ICU stay
 
- MRC Scale at ICU discharge
 
- Alive status at ICU discharge
 
- Duration of hospitalization
 
- Alive status at hospital discharge
 
- BMI at hospital discharge
 
 |

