## INVESTIGATION SCHEDULE

| Study Periods                                    | Screening and Patient information | Consent (ICF) + inclusion | Intervention                          | Follow-up                            |
|--------------------------------------------------|-----------------------------------|---------------------------|---------------------------------------|--------------------------------------|
| Visit                                            | 0                                 | 1                         | 2-17 (max)                            | 18-19                                |
| Time (hour, day, week)                           | -2 to -1 day                      | 0                         | From inclusion day during max 15 days | ICU discharge and Hospital discharge |
| Inclusion and exclusion criteria                 | X                                 |                           |                                       |                                      |
| Patient or legal representative Information      | X                                 |                           |                                       |                                      |
| Patient or legal representative consent          |                                   | X                         |                                       |                                      |
| Randomisation                                    |                                   | X                         |                                       |                                      |
| Demographics                                     |                                   | X                         |                                       |                                      |
| Anthropometrics                                  |                                   | X                         | X                                     | X                                    |
| Details of hospitalisation                       |                                   | X                         |                                       |                                      |
| Diagnosis                                        |                                   | X                         |                                       |                                      |

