### 5.4 Safety Outcomes

Hypoglycaemia

- Overall number and percentage of mild ( $\leq 3.2$  mmol/l), and severe ( $\leq 2.2$  mmol/l) hypoglycaemic events per patient and in the study.
- Number and percentage of mild ( $\leq 3.2$  mmol/l), and severe ( $\leq 2.2$  mmol/l) hypoglycaemic events due to non-compliance (only in intervention arm)

Hyperglycaemia ( $> 8.5$  mmol/l)

- The time taken to normalize blood glucose will be the time from enrolment in the study to the time of the first of two consecutive BG measurements  $\leq 8.5$  mmol/l

- Percentage of time in the ICU with hyperglycaemia (BG > 8.5 mmol/l) before and after normalization per patient and in the cohort.
- Percentage of time in the ICU with hyperglycaemia (BG > 8.5 mmol/l) before and after normalization per patient and in the cohort due to non-compliance (only in intervention arm)
- Number of hyperglycaemic episodes after normalization per patient and in the cohort
- Number of hyperglycaemic episodes after normalization per patient and in the cohort due to non-compliance (only in intervention arm)

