### 7.2 Recruitment and screening

#### 7.2.1 Intervention and control groups

Screening for inclusion into the intervention and the control groups will be done once a day (Monday to Friday) expect for the run-in phase. If more patients respect the eligibility criteria, priority will be given to people whose relatives can be reached at first. Eligible and consent patients will be randomized to either intervention group or control group. A deadline of 24 hours will be given to the legal representative or to the independent physician after presentation of the study to give or not their consent. For patients, once they are capable of consenting, a 48-hour delay after presentation of the study will be given. Before inclusion, all patients are treated according to the ICU- Geneva Protocols.

We will perform a “run-in phase” for the first 3 patients randomized in the intervention group. For these patients, we will ensure that the user asks for one advice in GS2 after each blood glucose measurement. Daily, one of the co-investigators will extract the GS2 data and check that all the advice given concerning insulin and glucose are correct according to GS2 predefined settings and if these are clinically acceptable. After the run-in period, if the GS2 recommendations are considered clinically acceptable, the control will be spaced at once a week. In the event of problems noted, the daily control will be maintained.

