#### 11.4.3 Secondary Analyses

For secondary outcomes, we will apply multiple regression models with adjustment on stratification variables and some prespecified variables.

- All continuous variables will be compared between the two study groups using either Student t test or Mann-Whitney nonparametric test; categorical variables will be compared using either Chi-2 test, or Fischer exact test, depending on application criteria.
- Count data (number of hyperglycemic episodes) will be compared using Poisson regression model or if data are over-dispersed, negative binomial regression models.
- Binary outcomes (protein goal achievement, caloric goal achievement) with repeated measurements will be analyzed using mixed-effects logistic regression models.
- Continuous outcomes with repeated measurements will be analysed using mixed-effects linear regression models.

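### The percentage of time with hyperglycaemia is divided by the whole ICU stay although glucose is recorded only in the study window, and normalisation is defined in two ways

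*Protocol*

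**What the plan says.** **Denominator.** Section 9.2.4 treats each glucose value as constant until the next and gives the percentage of ICU time with hyperglycaemia as "defined as cumulative time with BG > 8.5 divided by the time spent in the ICU". The outcome is reported before and after normalisation, but only this one denominator is given.

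**Recording window.** The synopsis heads the glucose and other daily data "Daily data from inclusion day (maximum follow up of 15 days". The investigation schedule marks glycaemia only in the intervention column, timed "From inclusion day during max 15 days". Follow-up can stop sooner; for the control group the synopsis says "The maximal follow-up is of 15 days or when he/she starts eating (voluntary feeding", and the intervention group has the same limits. ICU time also precedes inclusion: section 7.2.1 states "Before inclusion, all patients are treated according to the ICU- Geneva Protocols", and the schedule puts screening one to two days before inclusion.

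**Other denominators.** Section 5.1 divides time in target by the span from the first glucose measurement to 2 hours after the last. Section 5.3 describes the enrolment period as the ICU stay capped at 15 days.

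**Normalisation.** The synopsis has "Time to normalize blood glucose (2 values between 5.0 and 8.5 mmol/l as indicator for normalization". Section 5.4 takes "the time from enrolment in the study to the time of the first of two consecutive BG measurements" at or below 8.5 mmol/l. Section 9.2.4 likewise uses two consecutive values at or below 8.5. Neither body section sets a lower bound.

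**The concern.** The numerator can grow only while glucose is recorded. The denominator also counts ICU days before inclusion, after day 15 and after oral feeding starts, so those days are scored as free of hyperglycaemia. Length of ICU stay is partly determined after randomisation, so it need not be balanced between arms. The arm with longer stays outside the window would look better with identical glucose control. Reducing hyperglycaemia belongs to the safety objective (synopsis and section 4.4), and the resulting percentage cannot be read alongside time in target, which rests on monitored time.

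The normalisation rule fixes three things: time to normalise, the split of the percentage into before and after, and the number of later hyperglycaemic episodes. With two rules in the protocol, two analysts could report different results from the same data.

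**Working it through.** **The plan's own figures.** The protocol states no figure for the hyperglycaemia percentage. Its one computed figure nearby, 71 per group (section 11.2: difference 10, SD 21, 80% power, two-sided 5%), reproduces: the t-based solution is 70.2, rounded up to 71. It does not bear on this point.

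**1. Size of the dilution.** Let p be the true percentage within the recorded window, W the window and T the ICU stay. Hours above 8.5 are p × W, so the reported percentage is p × W / T. The documents give only an expected stay of at least 72 h, screening at day −2 to −1 and the 15-day cap. The values of p, T and time to inclusion below are therefore assumptions, with p = 30% throughout.

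| ICU stay T (days) | Inclusion after (days) | Recorded W (days) | W / T | Reported % |
|---|---|---|---|---|
| 3 | 0 | 3 | 1.00 | 30.0 |
| 3 | 1 | 2 | 0.67 | 20.0 |
| 3 | 2 | 1 | 0.33 | 10.0 |
| 10 | 2 | 8 | 0.80 | 24.0 |
| 10 | 2 | 5 (oral feeding) | 0.50 | 15.0 |
| 20 | 2 | 15 (cap) | 0.75 | 22.5 |
| 25 | 2 | 15 (cap) | 0.60 | 18.0 |
| 30 | 2 | 15 (cap) | 0.50 | 15.0 |

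The factor runs from 0.33 to 1.0 and never exceeds 1, so the error is always towards less hyperglycaemia.

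**2. A difference made by stay alone.** Take two patients with the same 15 recorded days and 30% of that time above 8.5. Stays of 20 and 25 days give 30 × 15/20 = 22.5% and 30 × 15/25 = 18.0%, a gap of 4.5 points with identical glucose. Divided by recorded time, both are 30%.

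**3. The two normalisation rules on one series.** Illustrative glucose every 2 h from 0 h: 11, 9.2, 4.6, 4.1, 9.0, 7.8, 7.2 mmol/l. The synopsis does not say which of the two values sets the time; the first is assumed here, as in section 5.4.

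- Body rule (two consecutive values ≤ 8.5): met by 4.6 and 4.1, so normalisation is at 4 h. The later 9.0 counts as one hyperglycaemic episode.
- Synopsis rule (two values 5.0 to 8.5): met by 7.8 and 7.2, so normalisation is at 10 h. There is no later episode.

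With the section 5.1 window (0 h to 12 + 2 = 14 h), time above 8.5 is 2 + 2 + 2 = 6 h, or 6/14 = 42.9% under either rule. The split is different:

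- Body rule: 4/4 h = 100% before and 2/10 h = 20% after.
- Synopsis rule: 6/10 h = 60% before and 0/4 h = 0% after.

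**The case against.** **The denominator may be loose wording.** Section 5.3 equates the enrolment period with the ICU stay up to 15 days, so the authors may have meant that here. Intent to count unmonitored days as hyperglycaemia-free is not shown, and that stands. However, section 9.2.4 omits the cap, and duration of ICU stay is collected as a separate variable, so someone following the text would probably use it. Even the capped ICU stay would not exclude time before inclusion or after oral feeding.

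**Perhaps all ICU glucose is used.** Section 9.3.2 reports baseline data back from ICU admission, but no serial glucose record before inclusion is stated. If there were one, hyperglycaemia from before randomisation would enter the treatment comparison.

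**Stronger readings that the documents do not support.**

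- A reader might infer that all hyperglycaemia outcomes are wrong by construction. Only the percentages use this denominator, and only patients with ICU time outside the window are affected.
- A reader might show the effect with equal hours above 8.5, say 36 h, in stays of 8 and 12 days (18.75% v 12.5%). Both stays lie under the 15-day cap. If recording runs to discharge and inclusion comes after 1 day, monitored time itself gives 36/(7 × 24) = 21.4% and 36/(11 × 24) = 13.6%, a wider gap. That example does not isolate the error.
- A reader might say that the body rule rewards overshoot into hypoglycaemia. It has no lower bound, but section 5.4 counts hypoglycaemia (≤ 3.2 mmol/l) separately, and an outcome about values above 8.5 may reasonably end at 8.5.
- A reader might conclude that the synopsis range must be the right rule. Section 8.1.2 calls 4.0 to 5.5 mmol/l spontaneously normal, and sections 5.4 and 9.2.4 agree with each other. The documents support reconciling the rules, not choosing either one.
- A reader might infer that patients who never normalise drop out of the comparison, because section 11.4.3 says "All continuous variables will be compared between the two study groups using either Student t test or Mann-Whitney nonparametric test". That section is introduced for secondary outcomes, whereas time to normalise is a safety outcome. No text assigns it this test, and the handling of such patients may be in a statistical analysis plan not seen here.

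**Conclusion.** The denominator point holds for the percentage-of-time outcomes. Followed as written, section 9.2.4 understates hyperglycaemia by the factor recorded window / ICU stay whenever the stay extends outside the window. Direction and formula follow from the text. The size rests on assumed stays: 30% becomes 22.5% or 18.0% for 20 or 25 days, and between 10% and 30% across the scenarios tabulated. The primary outcome, time to normalise and episode counts are untouched by it.

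The normalisation point is a contradiction between the synopsis and the body, not a miscalculation. It leaves time to normalise, the before/after split and the later episode count ambiguous until one definition is chosen. The overall percentage does not depend on it.

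**What to change.** 1. In sections 5.4 and 9.2.4, divide time above 8.5 mmol/l by the monitored time of section 5.1, stated as first study glucose measurement to 2 h after the last.
2. Divide the part before normalisation by monitored time before it, and the part after by monitored time after it. State that a patient with no monitored time in one of the two periods has no percentage for that period.
3. Reconcile the synopsis with sections 5.4 and 9.2.4 to a single definition of normalisation, including whether the values must be consecutive and which value sets the time. Do this before the analysis.

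The cost is protocol wording and minor programming, with no new data. The downside is that the reported hyperglycaemia percentage becomes less favourable.
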